## Abstract

**Background:**

Child maltreatment has a pervasive, detrimental impact on children’s wellbeing. Despite a growing focus on prevention through school based education, few programmes adopt a whole- school approach, are multi-component, seek to address all forms of maltreatment, or indeed have been robustly evaluated. This paper describes a cluster randomised controlled trial designed to evaluate a school based child maltreatment prevention programme: ‘Keeping Safe’ in primary schools in Northern Ireland. The intervention has been designed by a non-profit agency. Programme resources include 63 lessons taught incrementally to children between four and 11 years old, and is premised on three core themes: healthy relationships, my body, and being safe. There are programme resources to engage parents and to build the capacity and skills of school staff.

**Methods/design:**

A cluster Randomised Controlled Trial (RCT) will be conducted with children in 80 schools over a two-year period. The unit of randomisation is the school. Schools will be allocated to intervention or wait-list control groups using a computer-generated list. Data will be collected at three time points: baseline, end of year one, and end of year two of programme implementation. Primary outcomes will include: children’s understanding of key programme concepts, self-efficacy to keep safe in situations of maltreatment, anxiety arising from programme participation, and disclosure of maltreatment. Secondary outcomes include teachers’ comfort and confidence in teaching the programme and parents’ confidence in talking to their children about programme concepts.

**Discussion:**

This RCT will address gaps in current practice and evidence regarding school based child maltreatment prevention programmes. This includes the use of a whole- school approach and multi-component programme that addresses all maltreatment concepts, a two-year period of programme implementation, and the tracking of outcomes for children, parents, and teachers. Methodologically, it will extend our understanding and learning in: capturing sensitive outcome data from young children, adapting and using standardised measures with children of different ages, the use of school level administrative data on staff reports/children’s disclosure of maltreatment as behavioural outcomes, and the conduct of complex trials within the busy school environment.

**Trial registration:**

ClinicalTrials.gov: NCT02961010 (Retrospectively registered 8 November 2016).

## Background

Child maltreatment remains a significant global problem [1, 2]. Prevalence estimates indicate that 12.7% of children experience sexual abuse, 22.6% physical abuse, 36.3% emotional abuse and 16.3% physical neglect [3]. While this data concerns over one billion children aged between two and 17 years worldwide, these self-report estimates are considered to under-represent children’s experience; up to 30 times in the case of sexual abuse and 75 times in cases of physical abuse [4, 5]. Children with disabilities are at greater risk [6]. Thirty-five per cent of children experience bullying while 15% report experiencing cyber-bullying [7], which is also considered to be underreported [8]. Moreover, many children experience multiple types of maltreatment across their childhood, perpetrated by different people in different settings and contexts [9]. Trend data indicates increased reporting of emotional abuse and neglect, as well as sexual abuse carried out online or using digital technology, and abuse perpetrated by other children [10–14].

Maltreatment experiences have been shown to have pervasive detrimental impacts on health and wellbeing outcomes in the short and longer term. This includes relationship, reproductive and sexual behaviour disorders [15], suicide, bi-polar disorders, and alcohol and drug abuse [16]. Children who experience physical abuse, sexual abuse or neglect are more likely to develop depression and anxiety in adulthood [17] while experiencing emotional maltreatment in childhood is significantly associated with developing severe, early onset chronic depression in adulthood [18]. Children living with domestic violence are also at greater risk of experiencing these other forms of maltreatment [19]. Furthermore, experiencing school bullying and cyberbullying in childhood is associated with adult drug use [20], stress and suicide ideation [14]. Such experiences and their impact have been shown to have significant financial costs to the individual as well as society, in terms of healthcare, social care, education, criminal justice and lost productivity [21–23]. The most recent research reported in the United Kingdom estimates the average lifetime incidence cost of non-fatal child maltreatment by a primary caregiver at £89,390 [24].

### Prevention – School based programmes

Acknowledgement of the global prevalence, impact and costs of child maltreatment has led to a greater focus on prevention, and indeed school based prevention within the context of a public health framework, which seeks to address risk factors at the level of community and society as well as the individual child [25–28]. Despite the development of such school based programmes in high income countries over the past 40 years, research confirms significant gaps in practice and evidence [28–32].

Significantly, the majority of these programmes published in the research literature have been developed in the United States, Canada, Australia and New Zealand [29, 32]. The majority are classroom or curricular based as distinct from ones that focus on the whole school/organisation, are of relatively low dose [29, 30], focus on one type of maltreatment and are considered to lack coherence and breadth [12, 28, 33]. Moreover, these programmes are more likely focussed on building protective knowledge, awareness and skills of older children/young adults. It is reported that less than 10 % of inter-personal/relationship violence prevention programmes target elementary or middle school children [14, 33].

Overall, evidence indicates that school based prevention education programmes concerned with child sexual abuse [29], domestic abuse [30] and relationship and dating violence [32, 33] can lead to significant improvements in protective knowledge and attitudes in the short term. Significant behavioural outcomes were reported only in a small minority of programme evaluations concerned with bullying perpetration and victimisation [31, 34], perpetration of sexual violence [33] and disclosures of sexual abuse [29]. Methodological shortcomings in the evaluation of programmes have led to a lack of evidence as to whether school based prevention programmes actually reduce maltreatment [35]. More rigorous evaluation is required to address this question of effectiveness [13, 29, 30, 33, 36, 37] and should include the use of experimental designs [29, 35], appropriate standardised validated measures [14, 26, 30–32], measurement of behavioural outcomes [28, 29, 32, 33, 35], exploration of negative/adverse effects and should include follow up in the longer term [29, 32].

This paper concerns the evaluation of a comprehensive multi-component whole school maltreatment prevention programme ‘Keeping Safe’, developed in Northern Ireland. Programme development, led by a non-government agency, engaged local experts and key stakeholders in the development of a systematic logic model (see Fig. 1) informed by the principles associated with effective prevention interventions [38, 39], and a review of international research evidence and practice [12, 28, 29, 31–34, 40, 41], which sought to identify effective components of school based maltreatment prevention programmes and gaps in current practice. Moreover, local evidence captured through a comprehensive needs assessment with stakeholders in Northern Ireland [42–46] was also used to inform the development of a programme model that is culturally appropriate and attuned to the child protection practice environment that exists in Northern Ireland [25, 26, 30].

**Fig. 1 Fig1:**
[figure not shown]
Logic Model: Keeping Safe programme for children 4–11 years

### Aim

The aim of this study is to conduct a randomised controlled trial to determine the effectiveness of the *Keeping Safe* programme.

### Objectives

#### Primary objectives

To determine if exposure to the *Keeping Safe* programme impacts:children’s self-reported knowledge and understanding of the following keeping safe concepts: bullying, neglect, physical, emotional, domestic and sexual abusechildren’s self-reported self-efficacy to keep safe in situations of bullying, neglect, physical, emotional, domestic and sexual abusechildren’s self-reported skills as measured by the proxy skills measure ‘What If Situations Test’ to keep safe in situations of abuse/maltreatmentchildren’s disclosure and telling/ staff observation as measured by school level administrative safeguarding data including concerns noted, disclosures made, referralschildren’s self- reported anxiety

#### Key secondary objectives

To determine if engagement with the Keeping Safe programme impacts:teachers’ self-reported knowledge in teaching keeping safe messagesteachers’ self-reported confidence and comfort in their own skills to manage sensitive issues in relation to Keeping Safe in the classroomparents’ self-reported knowledge of and confidence to communicate with their child about keeping safe messagesparents’ self-reported current and future confidence to communicate with their child about keeping safe messages

#### Further secondary objectives

To determine:if changes in children’s knowledge and understanding vary with reported whole school level programme implementation, and classroom level programme implementationhow school context factors such as size, sector and management type, and teaching context factors; reported teacher access/use of continuing professional development training and resources and reported teacher knowledge, comfort and confidence in teaching keeping safe messages impact on children’s knowledge, understanding and skills, disclosures/referralshow parent characteristics; personal (gender) parenting profile (age of children, no of children) and home context (postcode) factors impact on children’s knowledge, understanding and skills, disclosures/ referralshow school context factors such as size, sector and management type, and professional experience factors (length of teaching service, nature of role in school) impact on teacher knowledge in teaching keeping safe messages, and confidence and comfort in their own skills to manage sensitive issues in relation to Keeping Safe in the classroomif access to, and use of the continuing professional development training and resources specifically designed for the Keeping Safe programme impact on teachers’ knowledge in teaching keeping safe messages and their confidence and comfort in their own skills to manage sensitive issues in relation to Keeping Safe in the classroomif implementing the Keeping Safe programme leads to change in school ethos/climate, and if this differs across schoolshow personal (gender) parenting profile (age of children, no of children, relationship to child) and home context (postcode) factors impact on parents’ knowledge of and confidence to communicate with their child about keeping safe messages

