## Methods

The evaluation will consist of three rounds of data collection: pre-assessment (baseline), post-assessment one (1 year after baseline) and post-assessment two (2 years after baseline). Data will be collected from children using a composite survey comprising existing and adapted standardised measures across the keeping safe concepts of bullying, physical, sexual, emotional and domestic abuse and neglect as well as anxiety. The content and administration of the survey (online and paper versions available) have been tailored to ensure age and developmental appropriateness and several different versions will be used with different age groups.

Children in Primary four through to Primary seven (ages seven to eleven) will complete online versions of the surveys. Children in Primary three (age six) will complete a paper version in line with their psychomotor development. All children’s surveys consist of self-report measures and will be completed under classroom test conditions supported by classroom teachers and learning assistants. ‘A Guide to Evaluation for Teachers’ booklet will be provided to all classroom teachers to standardise the data collection process across all schools and support school staff collect data from children on these sensitive issues in a manner that safeguards the welfare of the children and is child friendly. The youngest children in Primary one and Primary two (ages four to six) will complete their surveys in one-to-one interview-style sessions with trained volunteers from the non-profit agency schools’ service. Additional school-level administrative behavioural outcome data will be collected via school survey children’s disclosure / teacher reports of children’s maltreatment experiences.

All classroom teachers will be invited to complete a self-report survey with online and paper versions available. Fidelity data on completion of the blended package of training will be collated from the analytics function on the e-learning training programme. Self-reported fidelity to programme implementation in the classroom will be collated using a fidelity monitoring form. Information on school context (size, sector, management type) will also be collected from school administrative data.

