### Confidentiality

All outcome data will be identified by a unique ID only to ensure participant confidentiality. The unique IDs will also be used to enable matching of data across the timepoints of the trial. An electronic file containing participant names and unique IDs will be stored on a secure network to which only the evaluation team will have access. No identifying information will be recorded on completed data forms. All data collected will be stored anonymously with categorical labels being used to identify according to stakeholder group, school type, school sector, age of pupil, rural urban school. Categorical variables will be held separately to ensure that the statistician is unable to identify individual cases or responses within the data set.

In accordance with agency ethics guidelines, all completed forms (online and paper) will be reviewed for child protection concerns. If a concern or disclosure is identified, the concern, along with the unique ID will be passed to the Programme Development and Implementation Lead who will decide the action required. If necessary, the unique ID can be used to identify the child to whom the concern relates in order to facilitate contact with the child’s school and ensure appropriate safeguarding procedures are put in place. All participants will be made aware of this prior to the start of the evaluation. Any documentation containing identifying personal information, including consent forms will be stored in a locked cabinet to which only the evaluation team will have access. Results from the trial will be reported in a way that ensures no individual school, teacher, parent or child is identifiable.

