## Discussion

This trial seeks to rigorously evaluate the effectiveness of the Keeping Safe programme that will be taught to children aged between four and 11 years in 80 primary schools across Northern Ireland. This programme will be evaluated in the first cluster randomised controlled trial of a school-based child maltreatment prevention programme in Northern Ireland, Ireland and the United Kingdom. Keeping Safe is a novel maltreatment prevention programme in that it adopts a ‘whole school’ organisation model with components targeting children, staff, parents and the whole school community. Moreover, it seeks to address all forms of maltreatment and includes content on neglect, as well as sexual abuse carried out online or using digital technology, and perpetrated by other children, emerging areas often not included in other programmes [22, 26, 28].

Randomisation will occur at school-level and outcome data will be collected at multiple time points: baseline (T0), end of year one of programme implementation (T1), and end of year two of programme implementation (T2). We hypothesise that children in the intervention schools (at T2) will demonstrate increased knowledge of key programme concepts as well as increased self-efficacy and skills to keep safe in situations of maltreatment. We are seeking to use a proxy measure of children’s skills (What If Situations Test) [60] and school level data on children’s disclosure of maltreatment to measure behavioural outcomes [35]. We also hypothesise that teachers in intervention schools (at T2) will report increased levels of comfort and confidence when teaching programme concepts while parents of children in these schools will report increased comfort and confidence in talking to their children about programme concepts. Further to this, we hypothesise that there will not be an increase in children’s anxiety (at T2), as a result of taking part in the trial [29, 33].

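### The objective relating parent characteristics to children's disclosures and referrals needs family-level data, but the only disclosure source described is at school level (minor)

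*Protocol article*

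**What the plan says.** Under Further secondary objectives, the protocol article asks how "parent characteristics; personal (gender) parenting profile (age of children, no of children) and home context (postcode) factors impact on children’s knowledge, understanding and skills, disclosures" and referrals. A neighbouring objective asks the same of school context (size, sector, management type) and of teaching context. The latter covers use of training and how "reported teacher knowledge, comfort and confidence in teaching keeping safe messages impact on" the same list of outcomes.

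The article describes the disclosure outcome in these places:

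- Primary objectives: disclosure and staff observation are assessed "as measured by school level administrative safeguarding data including concerns noted, disclosures made" and referrals.
- Methods: "Additional school-level administrative behavioural outcome data will be collected via school survey".
- Discussion: the trial uses "school level data on children’s disclosure of maltreatment to measure behavioural outcomes".
- The Discussion part of the Abstract likewise calls these data school-level and administrative.

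The Confidentiality section adds that "All outcome data will be identified by a unique ID only to ensure participant confidentiality" and that "The unique IDs will also be used to enable matching of data across the timepoints of the trial".

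**The concern.** A parent's gender, the number and ages of the children and the home postcode are attributes of a family. They vary mostly among families within one school. To learn whether they bear on disclosure, each disclosure or referral has to be attributable to a child whose family attributes are known. The article describes a disclosure outcome that comes from the school, with no such attribution.

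If the objective is followed with the data as described, the analyst has one workable route: average the responding parents within each school and relate that average to the school's disclosure figure. Reporting the result as an impact of parent characteristics would be an ecological inference. An association between schools can differ in size, and even in sign, from the association between families within a school. Here it would also depend on which parents answered the survey.

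**Working it through.** The plan gives no power or precision figure for this objective, so there is nothing of its own to reproduce. The detectable differences under Sample size concern the comparison between arms.

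**Step 1. Level of each variable, as described.**

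| Variable | Source in the article | Level |
|---|---|---|
| Parent gender, age and number of children, postcode | Parent survey | Parent or family |
| Teacher knowledge, comfort, confidence | Teacher survey | Teacher |
| School size, sector, management type | School administrative data | School |
| Knowledge and skills | Child survey | Child |
| Disclosures, concerns, referrals | School survey of administrative safeguarding data | School |

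**Step 2. Search for a child-level route to disclosure.** The child measures cover bullying frequency, knowledge of sexual abuse, of domestic abuse and of neglect, anxiety, responses to scenarios, and self-efficacy. None asks whether the child has disclosed maltreatment. The unique ID has two stated uses: matching across timepoints, and tracing a child when a completed form raises a protection concern. The second is a safeguarding procedure and yields no outcome variable. Neither use ties a school's safeguarding records to a child's or a parent's survey.

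**Step 3. What can be estimated.** Let y_j be the disclosure figure for school j and x_ij the characteristic of parent i in school j. Write x_ij as the school mean x̄_j plus a deviation (x_ij − x̄_j). With y known only at school level, the deviations carry no information about it. Only the slope of y_j on x̄_j can be estimated; the within-school slope, which is what the parent objective asks about, is not identified. A multilevel model does not change this, because the outcome has no variation within schools.

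**Step 4. Precision of the between-school analysis.** Inputs: 80 schools (about 40 per arm, Sample size), 80% power and 5% significance (same section). Two-sided testing is assumed, since the article does not state it. By Fisher's z:

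r_min = tanh[(z_0.975 + z_0.80) / √(k − 3)]

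With k = 80: (1.960 + 0.842) / √77 = 2.802 / 8.775 = 0.319, and tanh(0.319) = 0.309, about 0.31.

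That equals 0.309² = 0.095, or about 9.5% of the between-school variance in disclosure explained by one predictor. This assumes all 80 schools return data and makes no adjustment for arm or other covariates.

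**The case against.** The strongest reply is that the article condenses a fuller protocol. It says school level, but it does not say that each school supplies one undivided total. A school survey could break records down by class or year group. All outcome data are said to carry a unique ID, and the 5% control rate under Sample size would suit a child-level event as well as a school rate. This stands in part. A reader might infer that disclosures are held only as school totals, but the text does not say so. A breakdown by class or year would still supply nothing about families, however. The conflict also lies between a stated objective and a stated source, so it is more than a detail left to another document. An analysis plan can choose a model but cannot create a link that data collection does not provide.

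The second reply concerns teachers, and it is largely right. A reader might infer that the teacher part fails in the same way. It does not. The Trial design section makes the school a unit of analysis, and the programme trains whole staffs. A school's mean teacher confidence or its training uptake is therefore a legitimate predictor of that school's disclosure rate. Only effects of the individual teacher or class are out of reach with the data as described.

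Third, it is tempting to present this as a fall from about 12,000 child surveys (80 × 150) to 80 units. The comparison says little. Those are surveys, not children with linked parent data, and the article gives no parent response rate. At the plan's intra-class correlation of 0.2 the design effect is 1 + 149 × 0.2 = 30.8, so for anything that varies between schools they are worth about 12,000 / 30.8 = 390 independent observations. The 0.31 is simply a property of 80 schools. It shows how coarse the remaining analysis would be and is not itself an error.

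Finally, the article spells out no analysis for this objective, so it does not commit anyone to misreport a school correlation. That limits the harm to a risk.

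**Conclusion.** The point holds in a narrow form. For parent gender, age and number of children and postcode, the objective asks a family-level question about disclosures and referrals that the data, as described, cannot answer. What remains is a between-school association over at most 80 schools, with a smallest detectable correlation of about 0.31 (80% power, two-sided 5%, full school participation). It would not support a statement about individual families. The same limit applies to effects of individual teachers or classes, but not to school-mean teacher or training measures.

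The conclusion rests on the article's repeated description of disclosure as school-level data and on the absence of any described link to a child or family. If such a link exists, the objective is sound and the description is what needs correcting.

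A reader might also infer that the disclosure comparison between arms, or the objectives as a whole, are undermined. The documents do not support that. Comparing arms on a school-level outcome is coherent in a school-randomised trial. Knowledge and skills are measured on children, and school size, sector and management type are proper school-level predictors. This is a minor point.

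**What to change.** 1. Remove disclosures and referrals from the parent-characteristics objective.
2. In the school and teaching-context objective, keep them, but analyse them only against school-level predictors: size, sector, management type, and school-mean teacher confidence or training uptake. Use a rate per enrolled pupil, and report the results as exploratory association and not as impact.
3. If disclosure records are in fact linked to the child or class, correct the school-level description of the outcome instead and state how the link is made. A link to the class alone would rescue class-level questions but not the parent question.

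The cost is a rewording of two further secondary objectives and the loss of the family-level disclosure question, which the described data could not answer. The knowledge, understanding and skills parts of these objectives, and all primary and key secondary analyses, stay as they are.
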